**Methods:**

We will use a standard pragmatic clustered (by school) randomised controlled superiority trial with an additional population-wide matched parallel control arm. Effectively, we will conduct three trials—one for each age/grade level. Each trial will be powered to assess the impact of the intervention on the age/grade groups independently: grade 2 (early primary, 7–8 years), grade 4 (mid primary, 9–10 years), and grade 6 (late primary, 11–12 years). Schools assigned to the treatment group will have all three grade levels (grades 2, 4, and 6) receiving the treatment (at least one class per grade); no classes in the schools assigned to the control group will receive the intervention. A minimum of 56 schools with an average cluster size of 19 children/class will be required to detect a minimum impact of 0.25 SD effect size at 80% power taking into account the clustered design with an intraclass correlation coefficient (ICC) of 0.05. This results in a total sample of 1064 per grade and thus 3192 students in total (56 schools per arm × 19 students in an average-sized class × three grade levels). Randomisation will occur on a 1:1 ratio, such that half of the schools (*n* = 28), and effectively about half of the students (*n* = 1596) will receive the intervention. The primary outcome will be improved self-regulation assessed at 6 weeks, 6 months and 12 months post the intervention. Longer-term secondary outcomes will include academic and wellbeing measures obtained through administrative data linkage to the National Assessment Program in Literacy and Numeracy (NAPLAN) outcomes and the Wellbeing and Engagement Collection (WEC) outcomes measures in the year following implementation (grades 3, 5, and 7). Follow-up via the South Australia Data Linkage Systems will allow for longer-term academic outcomes, mental health, school completion, criminal justice, and tax data.

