### Outcomes {12}

#### Primary outcome

The primary outcome will be the student’s Self-Regulated Learning at 6 months post-implementation of the intervention, as assessed by the student’s teacher using a brief rating scale consisting of 14 items.

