#### Secondary outcomes

Self-regulated learning will also be measured by the brief teacher-rated scale at 6 weeks and a student self-report measure with the same items will be utilised for grades 4 and 6. The student instrument will be implemented at 6 weeks, 6 months and 12 months post the intervention. Standardised academic achievement tests, Wellbeing and Engagement Collection (WEC) domains [27], school engagement, attendance and behaviour data will be obtained from the Department for Education through administrative data linkage.

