### Participant timeline {13}

Socialisation of the trial will be undertaken from November 2023, with school recruitment occurring at the same time. In the third school term, all intervention resources will have been fully adapted to the Australian context and modified to be appropriate for the three different grade levels.

Each of the four school terms is approximately 10 weeks. The teacher training will ideally be implemented late in the first term. The intervention will commence in all treatment schools across the three different grade levels in term 2 2024 (commences 29th April). We will provide video-based tutorials prior to each lesson of the intervention to remind teachers about the specific contents. Ideally, the intervention will be delivered from weeks 3 to 9 in terms 2, with flexibility given due to teacher sickness or other unforeseen disruptions.

Limited trial-specific measurements will be collected pre and post-intervention to ensure as low a burden on the school system as possible. Where possible, all data pertinent to the trial will be collected via administrative data collection. Depending on the assessment these are collected at different times of the year and for different grade levels. Trial participants will be linked to the Department’s administrative data systems with a longitudinal data set linked and generated for analyses. Extractions from the Department systems will occur once per term post-completion of the intervention, with impact determined on the different outcomes as the students age into and thus complete the various outcomes of interest (Fig. 1).

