## Statistical methods

### Statistical methods for primary and secondary outcomes {20a}

The primary analysis will use the intent-to-treat principle. Baseline balance will be checked between trial arms to see whether randomisation was successful. Estimation of treatment effects will be obtained from a generalised linear mixed model (GLMM) to produce the mean difference in scores for SRL intervention versus control. The GLMM will include a random effect for a cluster, and a random effect for the child taking account of the repeated measure design, a fixed effect for time, and use an exchangeable correlation structure of the appropriate variance–covariance matrix. The same analytical approach will be applied to secondary outcomes of interest. Longitudinal data collected for school cohort participants will be linked using student Education IDs. Student household characteristics may serve as predictors of interest in adjusted analyses.

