The primary objective of the trial is to adapt and implement the SRL intervention in Australian primary schools, assess its effects on self-regulated learning skills, and evaluate the intervention’s cost-effectiveness for potential scale-up in South Australia. Our primary outcome is a teacher-reported assessment of student’s self-regulated learning skills at 6 months after the intervention’s implementation. We selected this as the primary outcome measure, as it represents the earliest indication of the intervention’s impact. This measure is crucial for establishing whether any subsequent improvements in academic outcomes are attributable to enhanced self-regulated learning, rather than direct improvements in literacy and reading instruction. This assessment will be conducted near the end of the school year, before students move into different classes with new teachers, making it the latest feasible time point for evaluation. We acknowledge that teachers are not blinded to the trial arm due to the study design, which may introduce potential reporter bias. However, alternative methods, such as independent student observation or task-based assessments, were not considered to be feasible given the large sample and concerns from the Department for Education regarding the additional burden on teachers and students. The trial will also examine secondary outcomes, including academic achievement, attendance, behavioural problems, and various well-being domains. The study will involve a sample of at least 56 schools, with an average cluster size of 19 children per class, resulting in a total sample size of approximately 3192 students across three grade levels. Data will be collected through teacher-rated scales, administrative data linkage to educational outcomes, and the Wellbeing and Engagement Collection. Covariates, such as socioeconomic status and reading abilities, will also be considered in the analyses.

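### The stated repeated-measures model yields an arm difference averaged over visits, while the primary outcome is the 6-month teacher rating alone; the two differ if the effect changes between visits

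*Protocol article*

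**What the plan says.** The protocol article fixes one primary time point in two places. The Primary outcome section says: "The primary outcome will be the student’s Self-Regulated Learning at 6 months post-implementation of the intervention". The Discussion repeats it: "Our primary outcome is a teacher-reported assessment of student’s self-regulated learning skills at 6 months after the intervention’s implementation". The earlier teacher rating is placed under Secondary outcomes: "Self-regulated learning will also be measured by the brief teacher-rated scale at 6 weeks".

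The section Statistical methods for primary and secondary outcomes {20a} describes a generalised linear mixed model whose product is a single mean difference in scores, intervention versus control. Besides a random effect for cluster, its terms are "a random effect for the child taking account of the repeated measure design, a fixed effect for time, and use an exchangeable correlation structure". That section does not mention an arm-by-time interaction, a contrast at 6 months, or a restriction to the 6-month rating, and no other section does so.

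The abstract words the primary outcome differently: "The primary outcome will be improved self-regulation assessed at 6 weeks, 6 months and 12 months post the intervention". The specific hypotheses also list all three times for the teacher rating.

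**The concern.** A child random effect and a time effect have a purpose only if several assessments per child enter the model. Arm does not change over time within a child, so a model with arm and time but no interaction has one arm coefficient that must serve for every visit. The number reported for the primary outcome would then combine the 6-month rating with the 6-week rating, which the plan classes as secondary.

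Whether a five-hour programme has an effect that lasts is a central question of this trial, so an effect that changes between 6 weeks and 6 months is a realistic case. The 6-week rating is also made by unblinded teachers soon after they delivered the programme. A difference present only at that visit could carry a result labelled as 6 months. In the other direction, an effect that builds between the two visits would be diluted, and the power quoted for the primary outcome would not apply.

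**Working it through.** **Inputs from the protocol article** (abstract and Sample size {14}): k = 28 schools per arm, m = 19 pupils per class in a grade, ICC = 0.05, target effect 0.25 SD, power at least 80%.

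**Assumptions, not in the document:** two-sided alpha 0.05; within-child correlation between visits r = 0.7, with 0.5 to 0.8 as the range; a school effect that is the same at each visit; the effect trajectories below.

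**1. The plan's own figure.** Two means at 0.25 SD need 252 pupils per arm. The design effect is 1 + 18 × 0.05 = 1.9, so 252 × 1.9 = 478.8 pupils, or 478.8 / 19 = 25.2, rounded up to 26 schools per arm. The planned 28 per arm give 84.1% power (normal approximation) or 82.8% (t test on cluster means). The stated 56 schools therefore do deliver at least 80%, for an outcome at a single time point.

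**2. What the stated model estimates.** With balanced data, random intercepts and T visits, the generalised least squares arm coefficient is

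(1/T) × Σ over visits of (intervention mean − control mean at that visit).

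In one simulated data set with true effects 0.50 and 0, the visit-specific differences were 0.510 and 0.034. The fitted mixed model without interaction returned 0.272, which is their mean.

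**3. Standard error.** SE = √{ 2 × [ICC + ((r − ICC) + (1 − r)/T)/m] / k }.

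- T = 1: √{2 × [0.05 + 0.95/19]/28} = √(0.2/28) = 0.0845.
- T = 2, r = 0.7: √{2 × [0.05 + (0.65 + 0.15)/19]/28} = √(2 × 0.0921/28) = 0.0811.
- T = 2, r = 0.5: 0.0788. T = 2, r = 0.8: 0.0823.

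**4. Consequences for the two teacher ratings.** Power ≈ Φ(effect/SE − 1.96).

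| True effect, 6 weeks / 6 months | Model as written: estimate | Model as written: rejection, r = 0.7 (r = 0.8 to 0.5) | 6-month contrast: rejection |
|---|---|---|---|
| 0.30 / 0 | 0.15 | Φ(1.85 − 1.96) = 46% (45–48%) | 5% |
| 0.10 / 0.25 | 0.175 | Φ(2.16 − 1.96) = 58% (57–60%) | Φ(2.96 − 1.96) = 84% |
| 0.25 / 0.25 | 0.25 | Φ(3.08 − 1.96) = 87% (86–89%) | 84% |

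**5. Simulation check** (2,000 replicates, r = 0.7). For 0.30/0, the model as written gave a mean estimate of 0.149 and 46.3% rejection, against 5.2% for the 6-month contrast. For 0.10/0.25 it gave 0.177 and 58.6%, against 0.254 and 85.4%. Both agree with the formula.

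**The case against.** The strongest reply is that the list of terms is not exhaustive. It does not name the arm effect either, although the model must contain one, so its silence on arm-by-time does not prove exclusion, and an analysis plan could add the term. The section also does not say outright that the 6-week and 6-month ratings enter one model. This stands as a limit on certainty. It does not remove the mismatch: arm is implied by the stated mean difference, whereas nothing implies an interaction or a 6-month contrast. An analysis plan that supplied either would be changing the stated model.

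It can also be said that, under the abstract's wording, an average over assessments might be a legitimate target. That holds only if the Primary outcome section and the Discussion are set aside. The difference in wording also leaves open which visits would be averaged.

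The size of the effect on the results depends on assumed trajectories. That is correct. With a constant effect there is no bias and slightly more power.

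A reader might infer more than the document supports:

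- **A baseline row dilutes the estimate.** The participant timeline says "Limited trial-specific measurements will be collected pre and post-intervention", but nothing says that a pre-intervention rating of self-regulated learning is taken or would enter as an outcome row, and the schedule figure is not shown.
- **NAPLAN rounds are merged.** The section does say "The same analytical approach will be applied to secondary outcomes of interest", but the abstract describes NAPLAN and WEC outcomes in the year after implementation, and no passage pools rounds.
- **Any growing effect is missed.** Over three visits, effects of 0, 0.25 and 0.50 average to 0.25, the 6-month value.
- **The exchangeable structure is itself at fault.** No harm from it has been shown, and the remedy does not require replacing it.

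**Conclusion.** The point holds as a mismatch between stated passages: the analysis in {20a}, followed as written, does not estimate the primary outcome that the article defines. Settling the abstract's wording on 6 months would not cure it, because the model would still give a visit average.

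The averaging in balanced data follows from the model terms and does not depend on the assumed correlation. The harm is conditional on an effect that changes between 6 weeks and 6 months. In the two worked cases it is a 46% chance of a significant result with no 6-month effect, and a fall in power from 84% to 58%. These figures rest on the assumed alpha, correlation and trajectories; varying the correlation from 0.5 to 0.8 moves them by at most about two percentage points. The sample size itself is sound for a 6-month contrast.

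**What to change.** In Statistical methods {20a}, add an arm-by-time interaction with time as a categorical variable, and name the arm contrast at the 6-month teacher rating as the primary estimate. Analysing the 6-month rating alone with a random school effect would serve equally. Report the 6-week teacher rating as a separate secondary contrast. Carry the same wording into the analysis plan.

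This needs no new data and no more schools. If the effect is in truth constant, the 6-month contrast is slightly less precise than the average: a standard error of about 0.085 against 0.081, or 84% against 87% power at 0.25 SD.

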#### Longer-term secondary outcomes

Academic and wellbeing measures will be obtained through administrative data linkage by the Department for Education. This will include the National Assessment Program for Literacy and Numeracy (NAPLAN) [28] undertaken for all students in grades 3, 5, 7 and 9 and the Wellbeing and Engagement Collection which is undertaken annually for all students from grade 4 through to grade 12. Data can be linked longitudinally at an individual level.

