#### Covariates

Covariates will be obtained through linked education administrative data and will include the geographical socio-economic status of the primary residence of the child, parent's highest level of education, measures of reading abilities (as an indicator of pre-intervention cognition), disability status, school card status (poverty indicator), and prior school attendance records.

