### Sample size {14}

A sample of (at least) 56 schools will be required with at least one class in grade 2, grade 4 and grade 6, with an average cluster size of 19 children/class to detect a minimum impact of 0.25 SD effect size on the primary outcome with (at least) 80% power while accounting for the clustered design with an intraclass correlation coefficient (ICC) of 0.05. This results in a total sample of (at least) 56 clusters with an estimated 3192 students (or 1064/year level).

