## Assignment of interventions: allocation

### Sequence generation {16a}

Schools will be the level of randomisation and class the level of implementation. Randomisation will be stratified by socio-economic status blocks (using the Socio-Economic Indexes for Areas (SEIFA) indicator [29]) and metropolitan vs. non-metropolitan areas. The allocation sequence will be generated using computer-generated random numbers in Stata. Specifically, three block randomisation lists, one for each SES stratum will be generated with block sizes of 4 to ensure balanced allocation within each stratum. The advantage of numerous classes within the one school grade level has limited advantage for sample power due to the design effect associated with clustering. As such, at least one class per eligible grade level will be randomly selected for the intervention. Teachers will implement the intervention at the class level. The trial will be powered to assess the impact of the SRL intervention on three grades independently: grade 2 (early primary), grade 4 (mid primary), and grade 6 (late primary). The intervention will be implemented in literacy/reading lessons. Class lists will be provided by each of the participating schools for the process of randomisation. Note that schools in the treatment group may decide to implement the SRL intervention in more than one class within the school; however, only selected classes will be enlisted for the study. Schools in the control group will be required to not use the intervention (not even for non-enlisted classes).

We note that more than the required sample of 56 schools may wish to participate. As such we consider 56 as the minimum sample size, however the resultant study may be larger. Additionally, schools not meeting the eligibility criteria may still wish to participate in the study, for example, rural schools with multigrade classes. For such schools, we will include them as additional samples and block randomise accordingly.

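### The primary mixed model is specified without the randomisation strata or the linked pre-intervention covariates; this costs precision and makes the test conservative, although it causes no bias and the stated power is still met

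*Protocol article*

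**What the plan says.** - **Primary model.** Statistical methods {20a} describes a generalised linear mixed model with random effects for cluster and child, a fixed effect for time and an exchangeable correlation structure, giving the mean difference between arms. It carries the same approach over to the secondary outcomes. On adjustment it says only: "Student household characteristics may serve as predictors of interest in adjusted analyses".
- **Strata.** Sequence generation {16a}: "Randomisation will be stratified by socio-economic status blocks", together with metropolitan versus non-metropolitan location. It then describes three lists, one per SES stratum, in blocks of 4. The section on concomitant care {11d} adds stratification by the waitlist of the Department's existing support program.
- **Covariates.** The Covariates part of Outcomes {12} lists linked area SES, parental education, disability, school card status, prior attendance and "measures of reading abilities (as an indicator of pre-intervention cognition"). The Discussion says that covariates such as SES and reading will be considered in the analyses, without saying in which.
- **NAPLAN.** Longer-term secondary outcomes says that it is "undertaken for all students in grades 3, 5, 7 and 9" and that records can be linked over time for each child.

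**The concern.** Two separate losses follow if the model is run as described.

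1. **Strata omitted.** Stratified blocks force the arms to be alike on the stratum factors, so the true sampling variance of the treatment difference is smaller. A model without those factors still counts their variance as noise. Its standard error is then larger than the true one, its intervals are too wide and its test rejects too rarely under the null.
2. **Prognostic covariates omitted.** Here the standard error is honest but larger than it needs to be. Reading level and prior attendance are measured before the intervention and are already being linked, so the protocol pays for them without using them where they would help most.

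With 28 schools per arm, precision is limited. The protocol also plans to examine heterogeneity by grade and socio-economic position, and such contrasts usually need more precision than the main effect.

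**Working it through.** **Inputs from the protocol.** Sample size {14} plans "to detect a minimum impact of 0.25 SD effect size on the primary outcome with (at least) 80% power", an "intraclass correlation coefficient (ICC) of 0.05" and a sample "with an average cluster size of 19 children/class", in 56 schools. The Abstract gives 1:1 allocation with 28 schools in the intervention half, and 3192 = 56 x 19 x 3 confirms that 56 is the total.

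**Assumed inputs.** Two-sided alpha of 0.05. Share of variance explained (R2) between schools (R2b) and within schools (R2w), each from 0 to 0.5. The protocol gives neither.

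**Step 1: reproduce the plan's figure.** Two means at 0.25 SD and 80% power need 252 per arm. The design effect is 1 + 18 x 0.05 = 1.9. Then 252 x 1.9 = 478.8 per arm, and 478.8 / 19 = 25.2, so 26 schools per arm (52) by the normal approximation. With a t reference, 26 per arm gives 79.8% and 27 gives 81.3%, so 54 schools. The next multiple of the block size of 4 is 56, so the stated figure is reproduced.

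**Step 2: precision as planned.** The variance of a school mean is 0.05 + 0.95/19 = 0.05 + 0.05 = 0.10. SE = sqrt(2 x 0.10 / 28) = 0.0845 SD. Power at 0.25 SD is 84.1% (normal) or 82.8% (t, 54 df). The minimum detectable effect at 80% power is 0.241 SD (t).

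**Step 3: precision with adjustment.** The school-mean variance becomes 0.05(1 - R2b) + 0.05(1 - R2w). The t test has 49 df, which allows for five stratum terms.

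| R2b | R2w | SE (SD) | Power | Detectable effect (SD) |
|---|---|---|---|---|
| 0 | 0 | 0.0845 | 82.6% | 0.242 |
| 0.2 | 0 | 0.0802 | 86.4% | 0.229 |
| 0.3 | 0 | 0.0779 | 88.2% | 0.223 |
| 0.3 | 0.2 | 0.0732 | 91.7% | 0.209 |
| 0.5 | 0.5 | 0.0598 | 98.4% | 0.171 |

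For the fourth row: 0.05 x 0.7 + 0.05 x 0.8 = 0.075, and sqrt(2 x 0.075 / 28) = 0.0732. The first row shows the cost if the strata explain nothing: 82.8% falls to 82.6%, about 0.1 point before rounding.

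**Step 4: type I error when the strata are omitted.** If the strata explain 20%, 30% or 40% of the between-school 0.05, they account for 0.010, 0.015 or 0.020, which is 10%, 15% or 20% of the total 0.10. The ratio of reported to true SE is sqrt(0.10/0.09) = 1.05, sqrt(0.10/0.085) = 1.085 and sqrt(0.10/0.08) = 1.12. The type I error, 2[1 - Phi(1.96 x ratio)], is 3.9%, 3.4% and 2.8%.

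**Step 5: simulation.** School means were simulated with complete blocks of 4 in six assumed strata, 10,000 runs per scenario.

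| R2b | Type I error, strata omitted | Power, strata omitted | Power, strata included |
|---|---|---|---|
| 0.2 | 3.9% | 84.5% | 86.9% |
| 0.3 | 3.3% | 84.6% | 88.1% |
| 0.5 | 2.0% | 85.8% | 91.7% |

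With the strata in the model, the type I error stayed between 4.5% and 5.3%, and the reported SE matched the true one.

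**The case against.** The strongest reply is that this is a condensed article, that covariate lists often belong in the statistical analysis plan, and that saying a model will include certain terms does not exclude others. Even the treatment term is only implied. This stands in part: the text does not show that strata and covariates are ruled out. But the protocol describes its primary model, makes adjustment optional in the same section, and nowhere places the strata in any model. The Discussion's sentence is firmer and names reading ability, yet it does not tie covariates to the primary analysis.

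Several stronger readings are tempting and are not supported:

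- **That the result would be biased, falsely significant or underpowered.** Step 4 shows the opposite direction of error, and the unadjusted design meets its 80% target.
- **That the primary result is open to choosing covariates after the fact.** If the primary model has none, that risk falls on the secondary adjusted analyses. Sections {17a} and {17b} keep the analysts blinded to arm, which limits it further.
- **That the covariates exist for every child.** The Covariates text makes no claim of completeness.
- **That no baseline score is used.** Participant timeline {13} mentions limited measurements before the intervention, and the schedule figure is not available, so whether a baseline SRL rating is taken cannot be judged.
- **That prior NAPLAN would explain a given share of later NAPLAN.** The protocol has no figure for this, and the ICC of 0.05 is stated for the primary outcome only.

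**Conclusion.** The point holds as one of efficiency and calibration, not validity. As described, the primary model gives up precision that the design and the linked data already offer, and its standard errors do not reflect the stratification. If the strata explain 20-40% of the between-school variance, the type I error is about 3-4% rather than 5%. That share must not be read as 20-40% of the total variance of school means, of which it is only 10-20%. With R2b 0.3 and R2w 0.2, per-grade power would be about 92% against about 83-84% now, and the detectable effect about 0.21 SD against 0.24.

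These figures rest on assumed R2 values, on an analysis of school means at one time point as a stand-in for the full mixed model, and on complete blocks within six strata. If fewer factors were in fact used to stratify, the conservatism would be less.

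**What to change.** 1. Reconcile the strata first. Section {16a} names metropolitan status but describes only three SES lists, and {11d} adds the waitlist. Section {16a} also allows extra schools outside the eligibility criteria to be block randomised separately. State which factors were actually used.
2. State that the primary model includes fixed effects for those strata, plus prespecified pre-intervention reading level and prior attendance, with school card status and parental education as available.
3. For NAPLAN outcomes in the grade 4 and grade 6 cohorts, adjust for the prior NAPLAN score where it is linked. By the test's grade schedule, these children would ordinarily have sat it the year before. The grade 2 cohort has no earlier score.
4. Report the unadjusted model as a sensitivity analysis.

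The cost is a change of wording, a few degrees of freedom (about 0.1 power point if the strata explain nothing) and simple handling of missing covariates, for which section {20c} already plans imputation.
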